|                                                 | 
 
- the length of hospital stay
 
- the maximum flow rate of oxygen therapy (nasal or mask)
 
 
Secondary Criteria:
 
 
- the proportion of patients admitted to intensive care (among those who were in the conventional hospitalization department at baseline)
 
- Number of days alive without invasive ventilation in the first 28 days
 
- Number of days alive out of intensive care in the first 28 days
 
- Number of days alive out of hospital in the first 28 days
 
- Number of days alive without NIV or high-flow oxygen therapy in the first 28 days (for those who did not benefit at baseline)
 
- maximum flow rate of oxygen therapy over the first 28 days
 
                                                                                   |
| Experimental design                             | Prospective, randomized, open-label, multicenter study (stratified on the patient's status in ICU/out of ICU).                                                                                                                                                                                                                                                                                                                                                                                                                                                                                                                                                                                                                                                                                                                                                                                                      |

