### 3.2 Secondary Research Objectives

To show that daily prone placement (objective of at least 6 hours) in COVID patients with respiratory involvement requiring oxygen therapy of at least 3L/min decreases:

- the proportion of patients admitted to intensive care (among those who were in the conventional hospitalization department at baseline)
- the use of intubation
- the use of non-invasive ventilation or high-flow oxygen therapy (for those who were not already receiving it at baseline)
- length of ICU stay
- length of hospital stay
- the maximum flow rate of oxygen therapy (nasal or mask)

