### 4.2 Secondary endpoints

- The proportion of patients admitted to intensive care (among those who were in the conventional hospitalization department at baseline)
- Number of days alive without invasive ventilation in the first 28 days
- Number of days alive out of intensive care in the first 28 days
- Number of days alive out of hospital in the first 28 days
- Number of days alive without NIV or high-flow oxygen therapy in the first 28 days (for those who did not benefit at baseline)
- Maximum Flow Rate of Oxygen Therapy Over 28 Days

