## 6.1 Research Timeline

### 6.1.1 Inclusion visit.

For 18 months following the validation of the ethics committee, patients meeting the criteria and admitted to the COVID ward or intensive care in the 21 centers within the 11 hospitals in France and Mexico referenced for this study will be offered to participate in the study orally after verification of the inclusion and non-inclusion criteria and then a written consent will be collected. Notification of the patient's participation in this study will be listed in the patient's medical record.

We will collect:

**Socio-demographic data:** age, sex, weight, height, date of onset of symptoms, date of hospital admission

**Constants:** systolic blood pressure (SBP), diastolic blood pressure (DBP), heart rate (HR), body temperature, respiratory rate (RH), oxygen saturation, oxygen therapy flow.

Collection of the date of the last chest CT scan before inclusion with percentage of lung parenchyma involvement on CT images. Chest CT scan is not required for the study if the patient has not had one.

**Biology:** white blood cell counts, serum creatinine, D-Dimer, AST, and ALT (liver enzymes). This assessment will be collected, if it exists, made within the usual framework.

**Medical history:** chronic respiratory disease, cardiovascular disease, liver disease, diabetes and cancer or hematopathy under treatment.

Randomization will be done following the collection of written consent, via Cleanweb software.

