### 6.1.2 Follow-up visits

From this point on, patients in the interventional group (Group A) will be instructed to spend at least 6 hours on their stomach (PP). They will put themselves in the position. They will stand on their stomach with their head turned to the side and a cushion placed under the chest at their convenience and will regularly note the time spent in PP. They (or the nurse in charge) will have at their disposal a collection sheet and a pen.

Patients in the control group (Group B) will do as usual without external intervention on the positioning to be adopted.

For a maximum of 28 days, a daily reading of the

- Vital status
- Transfer to intensive care for patients included in a ward unit

- Use of intubation
- Use of an alternative ventilation technique (NIV, high-flow nasal oxygen therapy)
- Maximum Oxygen Therapy Flow Rate (Nasal or Mask)

At the end of the stay (maximum on the 28th day): we will collect

- Length of ICU stay
- Length of hospital stay

If the patient is discharged before day 28 (maximum duration of study participation)

- Your vital status will be searched for up to 2 months after discharge by phone call

The total duration of the study will be 19 months.

|                                       |                                                              |
|---------------------------------------|--------------------------------------------------------------|
| Length of Inclusion Period            | 18 months                                                    |
| Duration of participation of subjects | 28 days                                                      |
| Search for vital status               | Up to two months after discharge from hospital by phone call |

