## 7 SELECTION CRITERIA

### 7.1 Inclusion criteria

- Non-intubated adult COVID-19 patients (positive PCR or imaging: typical CT scan) requiring nasal oxygen therapy at a rate of at least 3 L/min to have a peripheral saturation greater than or equal to 95%
- Patient able to manage prone positioning on their own intellectually and physically
- Lack of limitation of therapies
- Patient affiliated to a social security scheme

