### ***Secondary Criteria***

For each parameter, the a posteriori probabilities will be described using different types of priors (non-informative or vague). The 95% credibility intervals will be calculated.

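### The 28-day maximum oxygen flow starts on Day 1 without separating out the entry flow, so the endpoint may have a floor at entry flow and lose sensitivity (not a bias)

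*Protocol*

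**What the plan says.** Section 4.2 of the protocol gives the endpoint as "Maximum Flow Rate of Oxygen Therapy Over 28 Days". The synopsis has "maximum flow rate of oxygen therapy over the first 28 days", and section 9.1 repeats the definition in similar words. None of the three says that the window opens after the baseline reading, defines a change from baseline, or restricts the population. The objective in section 3.2 is to show that prone positioning lowers "the maximum flow rate of oxygen therapy (nasal or mask").

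Other endpoints do take account of entry status. The primary endpoint counts events absent at randomisation. ICU admission is limited to patients on the ward at baseline. Days without NIV or high-flow oxygen are counted "for those who did not benefit at baseline".

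Eligibility (section 7.1) requires "oxygen therapy at a rate of at least 3 L/min". The inclusion visit (section 6.1.1) records "oxygen saturation, oxygen therapy flow". After randomisation, section 6.1.2 provides "For a maximum of 28 days, a daily reading of the" items that include maximum oxygen flow. The chronology table in section 6.1 ticks oxygen flow twice: at selection on Day 1 and in the visits from D1 to D28. Inclusion and randomisation are also on D1.

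For the analysis, the Secondary Criteria paragraph of section 13.1 says: "For each parameter, the a posteriori probabilities will be described using different types of priors (non-informative or vague"), with 95% credibility intervals. It names no covariate for any endpoint.

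**The concern.** A maximum over a window that contains the starting value can never be lower than that value. By eligibility, every patient here starts on at least 3 L/min. If the Day 1 reading is at or close to the entry flow, a patient who improves steadily from randomisation scores the flow that qualified them for the trial, and prone positioning cannot alter that score. Two patients, one weaned quickly and one held at entry flow, then score the same.

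The arm difference therefore comes only from patients whose later flow exceeds their entry flow in at least one arm. Meanwhile the spread in entry flow adds variance. A null result on this endpoint could reflect the floor and not the absence of an effect on later oxygen need.

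**Working it through.** **What the protocol gives.** It states no mean, SD, effect size or escalation rate for oxygen flow, so there is no figure of its own to reproduce for this endpoint. The maximum of 500 patients relates to the primary endpoint: 25% against 15%, with two-sided 5% and 1:1 allocation assumed, needs 250 per arm for power 0.800. It does not bear on this point, except that 250 per arm is used below.

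**Algebra, no assumptions on size.** Let B be the Day 1 flow, P the highest later flow and M = max(B, P). If P ≤ B under both arms, then M = B in both and that patient contributes zero to the arm difference.

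**Illustration 1.**
- The minimum of 3 L/min is from section 7.1.
- The ceiling of 15 L/min is assumed. Section 2.1.1 mentions it for the disease in general, not as an entry limit. Patients on high-flow oxygen (up to 60 L/min in section 2.1.2) are not modelled.
- B = min(15, 3·exp|N(0, 0.8)|).
- P = min(15, B·exp(N(μ, σ))). The median change exp(μ) − 1 is 0, +22% or +65% for μ = 0, 0.2 or 0.5.
- The treatment effect lowers the log change by 0.2 (assumed).
- Share kept = (arm difference in M) / (arm difference in P), computed before rounding. The r² column is the squared correlation of B with M in controls.

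| μ | σ | M = B | r² | diff in P | diff in M | kept |
|---|---|---|---|---|---|---|
| 0 | 0.3 | 52% | 0.87 | −1.06 | −0.46 | 43% |
| 0 | 0.5 | 52% | 0.70 | −1.03 | −0.54 | 52% |
| 0 | 0.8 | 52% | 0.48 | −0.92 | −0.54 | 58% |
| 0.2 | 0.3 | 29% | 0.77 | −1.18 | −0.80 | 68% |
| 0.2 | 0.5 | 37% | 0.58 | −1.12 | −0.74 | 66% |
| 0.2 | 0.8 | 43% | 0.40 | −0.97 | −0.63 | 65% |
| 0.5 | 0.3 | 9% | 0.61 | −1.30 | −1.20 | 92% |
| 0.5 | 0.5 | 20% | 0.43 | −1.19 | −0.98 | 83% |
| 0.5 | 0.8 | 30% | 0.30 | −0.99 | −0.74 | 75% |

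Entry flow thus explains 30 to 87% of the variance, and the maximum keeps 43 to 92% of the difference.

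**Illustration 2, a different model.** B is log-normal with median 5 L/min, held to 3–15. The later change is normal with SD 4 L/min, the true shift is −1 L/min, and flow is capped at 15. The share of controls whose later peak exceeds B is varied. Adjusted power uses the residual variance (1 − r²). Power is at 250 per arm.

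| share escalating | kept | M raw | M adjusted | P raw | P adjusted |
|---|---|---|---|---|---|
| 80% | 76% | 0.53 | 0.71 | 0.65 | 0.78 |
| 60% | 59% | 0.37 | 0.63 | 0.62 | 0.77 |
| 40% | 42% | 0.21 | 0.50 | 0.57 | 0.74 |
| 20% | 25% | 0.09 | 0.33 | 0.49 | 0.67 |

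Adjusting for entry flow raises power on either version. On the Day-1-inclusive maximum it stays below the adjusted post-baseline peak in every row, so adjustment recovers precision but does not remove the floor.

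**The case against.** - **The Day 1 reading may be post-randomisation.** Section 6.1.2 places the daily readings after randomisation, and the chronology table ticks selection separately from the visits. This stands in part. It cannot be said that the pre-randomisation flow is certainly in the maximum, because the protocol does not say which Day 1 value counts. A reading soon after randomisation would still lie near the entry flow.
- **Missing adjustment is silence.** Section 13.1 excludes no covariate, and an analysis plan that is not shown may name them. This stands: a reader might infer a decision not to adjust, and the protocol does not support that. The endpoint definition, however, is fixed in the protocol.
- **The endpoint fits the hypothesis.** Section 2.2 speaks of preventing deterioration, and a maximum measures worsening. An improving and a stable patient have both not worsened. That is fair, but a rise above entry flow would measure worsening more cleanly than a raw maximum carrying the entry spread.
- **The restricted endpoints are not true parallels.** A patient already in ICU cannot be newly admitted, whereas one on 6 L/min can still escalate. This stands, so the comparison shows only that entry status was considered elsewhere.
- **The inputs are assumed.** With a +65% median change the loss is slight to moderate (75 to 92% kept). This stands and limits any claim about size.

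**Conclusion.** The concern holds as a weakness in how one secondary endpoint is defined. If a Day 1 value at or near entry flow counts, the endpoint has a floor there and loses sensitivity. The direction is the same in every scenario of both illustrations. The size runs from slight to large, and the protocol cannot settle it: 43 to 92% of the post-baseline difference is kept in the first illustration and 25 to 76% in the second. Both rest on an assumed 3–15 L/min entry range, assumed escalation and an assumed effect.

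A reader might go further and infer that the endpoint mainly compares how ill the arms were at entry, or that it is biased. The documents do not support that. Randomisation balances entry flow in expectation, and chance imbalance is part of the ordinary uncertainty. In the first illustration the maximum exceeds entry flow in 48 to 91% of control patients. The primary endpoint and the stopping rules, which concern its odds ratio, are untouched.

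**What to change.** Reword the endpoint in the synopsis and in sections 4.2 and 9.1 as the highest oxygen flow recorded after randomisation through Day 28. Exclude the selection or inclusion reading but keep later Day 1 readings, so that genuine Day 1 escalation still counts; a fixed Day 2 start would discard it. State that the arm difference will be estimated in a model with oxygen flow at inclusion as a covariate. That value is already collected at the inclusion visit.

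Both parts are needed: the definition takes the entry reading out of the maximum, and the covariate recovers precision.

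The cost is wording only, with no new data or visits. Patients with no post-randomisation reading need a stated handling rule. A first reading taken shortly after randomisation will still sit close to entry flow, so some of the floor will remain.

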## 5 DESCRIPTION OF THE RESEARCH METHODOLOGY

### 5.1 Experimental design

Comparison of two positioning strategies to prevent respiratory complications related to COVID-19 respiratory infections

Randomized study, two comparison groups

**Group A:** interventional group: Patients will be instructed to spend at least 6 hours in the prone position (PP). They will put themselves in the position and regularly note (or the nurse in charge) the time spent in PP on a specific document provided by the research. Patients will lie on their stomach with their head turned to the side and a cushion placed under the chest at their convenience.

**Group B:** control group: Patients will not have any particular positioning instructions.

## 5.2 Number of participating centres (see list in addendum)

It is a multicenter research carried out in 12 hospitals in France.

### - Recruiting Centres

Conventional hospitalization services dedicated to the care of COVID-19 patients will receive patients who meet the inclusion criteria (non-intubated patients requiring 3L/min of O2 or more to obtain a peripheral saturation greater than 95%). The intensive care units will also include patients (either on simple oxygen therapy, on high-flow oxygen therapy, or on non-invasive ventilation) on these same criteria.

## 5.3 Description of measures taken to reduce and avoid bias

### 5.3.1 Subject Identification

Patients who will be offered to participate in the study should not be influenced by the assumption that the prone position would be more effective in improving their respiratory capacity compared to patients who will be given the choice of their positioning during medical management. This is why we have written an information note that makes sure not to influence patients who are not in the intervention group so that they keep the position of their choice without external interference in order to obtain results as relevant as possible.

### 5.3.2 In this research, the subjects will be identified as follows:

- Center No. (3 numerical positions) – I\_\_I\_\_I\_\_I
- number of selection of the person in the centre (4 numerical positions) - I\_\_I\_\_I\_\_I
- Initial last name - initial first name - I\_\_I/I\_\_I

This reference is unique and will be kept for the duration of the research.

### 5.3.3 Randomization

The patient randomization list will be drawn up according to a stratified randomization table by center and established by the F-Widal-Lariboisière clinical research unit.

Randomization will be done after verification of the inclusion and non-inclusion criteria, in the department where the patient has signed his consent (inclusion).

The investigator will perform randomization via Cleanweb software.

After getting to know the group, he will explain the strategy to the patient

**Group A:** interventional group: Patients will be instructed to spend at least 6 hours in the prone position (PP). They will put themselves in the position and regularly note the time spent in PP (or the nurse in charge) on a specific document provided by the research. Patients will lie on their stomach with their head turned to the side and a cushion placed under the chest at their convenience.

**Group B:** control group: Patients will not have any particular positioning instructions.

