## 13 STATISTICAL ASPECTS

### 13.1 Description of the planned statistical methods:

#### **Study size:**

This is a Bayesian study whose analysis will be based on the calculations of the a posteriori probabilities for a number of hypotheses. There is therefore no fixed sample size as in a frequentist analysis. The stop rules will be based on the probability calculations conditional on the data of an  $OR > 1$ , corresponding to a non-zero effect but also of an  $OR > 1.05$  corresponding to a more marked effect, but also on the probabilities of  $OR < 1$  ineffectiveness or of a marked deleterious effect  $OR < 0.95$  with respective probability thresholds set at 0.95, 0.80, 0.8, 0.75. Vague priors but adapted to Bayesian studies using ORs will be used. The maximum size of the study is set at  $N=500$  patients (based on the size of a frequentist study with a power of 80% to demonstrate a difference of 10%

between the 2 groups (i.e. 25% vs 15%). The simulations carried out show a high probability that the study will be conclusive after the inclusion of less than 300 patients.

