### ***Main criterion:***

The posterior probabilities of the primary endpoint will be calculated using different types of priors (non-informative or vague).

The following posterior probabilities will be calculated:

P (OR>1), corresponding to a non-zero effect of the prone position.

P (OR>1.05) corresponding to an effect that is already clinically interesting.

P (OR<1) corresponding to inefficiency of the prone position.

P (OR < 0.95) corresponding to a deleterious effect of the prone position.

The thresholds considered particularly interesting for the a posteriori probabilities described below are respectively equal to 0.95, 0.80, 0.8, 0.75.

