### ***Secondary analyses***

An analysis of the following subpopulations is planned a priori:

- Age >70 years
- Patients with NIV or high-flow oxygenation at baseline
- Patients included in intensive care or not

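### Stratification factor contradicts itself: ICU status in the synopsis, centre in section 5.3.3, with centre never defined

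*Protocol*

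**What the plan says.** The protocol describes the stratification in two places.

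- Synopsis, Experimental design: "Prospective, randomized, open-label, multicenter study (stratified on the patient's status in ICU/out of ICU". Centre is not named as a factor.
- Section 5.3.3: "The patient randomization list will be drawn up according to a stratified randomization table by center". ICU status is not named.

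Neither place refers to the other, and no other section says that both factors are used.

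On the analysis, section 13.1 (Main criterion) says "The posterior probabilities of the primary endpoint will be calculated using different types of priors (non-informative or vague". It then lists posterior probabilities for OR>1, OR>1.05, OR<1 and OR<0.95, and the stopping criteria use thresholds on these. No model, covariate or stratum is named, and the OR is not called unadjusted either. ICU status returns only among the planned subpopulations: "Patients included in intensive care or not".

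**The concern.** The randomisation list is fixed in the system before the first patient, so an analysis plan cannot settle afterwards which factor was used. As written, whoever builds the list cannot tell whether to use ICU status, centre or both.

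The protocol's own text gives reason to care about ICU status. Section 5.2 lets ICUs enrol patients on simple oxygen, high-flow oxygen or NIV alongside ward patients. Section 2.1.2 describes care that moves from oxygen to high-flow oxygen to intubation, and intubation is part of the primary endpoint. Section 2.3 refers to ICU and high-flow patients when it sets the expected event rate.

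If the list balances only within centres that mix both settings, the arms can differ by chance in their ICU share. This matters most at the early looks: efficacy and safety stopping are tied to the second interim analysis, and looks come every 50 patients. The OR that drives those rules is also not identified as marginal or conditional.

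**Working it through.** **1. What centre could mean**

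- The synopsis row on monthly inclusions per centre is answered per department; section 7.3 gives the same figure per centre.
- Section 6.1.1 has 21 centres in 11 hospitals in France and Mexico; section 5.2 has 12 hospitals in France.
- Section 5.3.3 places randomisation in the department where consent is signed.

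If each centre is one ward or one ICU, stratifying by centre also balances ICU status. If a centre is a hospital, it does not. The text permits both readings.

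**2. The plan's own figure**

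The maximum of N=500 is based on a study "with a power of 80% to demonstrate a difference of 10" percentage points, 25% vs 15%. Two-sided alpha 0.05 and 1:1 allocation are assumed here, because the protocol states neither:

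`n per arm = [1.960·√(2·0.20·0.80) + 0.8416·√(0.25·0.75 + 0.15·0.85)]² / 0.10² = [1.1087 + 0.4723]² / 0.01 ≈ 250`

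The total is 500, so the figure reproduces. Stratification plays no part in it.

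**3. Chance imbalance if the list does not balance ICU status**

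For ICU share f and N/2 patients per arm, the SD of the between-arm difference in ICU share is `√(4f(1−f)/N)`. The documents give no f, so a range is assumed.

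| f | N=100 | N=500 |
|---|---|---|
| 20% | 8.0 points | 3.6 points |
| 35% | 9.5 points | 4.3 points |
| 50% | 10.0 points | 4.5 points |

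With f=50% and N=150 the SD is 8.2 points. These are upper values: any centre that recruits from one setting only reduces them.

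A 10-point imbalance moves the crude risk difference by the imbalance times the ICU-minus-ward risk difference. With assumed control rates of 40% and 10% that is 0.10 × 0.30 = 3 points; with 35% and 15% it is 0.10 × 0.20 = 2 points. The SE of the crude difference at N=100 is `√(0.25·0.75/50 + 0.15·0.85/50)` = 7.9 points. The shift is visible but well inside sampling error.

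**4. Effect of putting ICU status into the model, N=500**

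The marginal rates are held at 25% and 15%.

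- Crude log OR = ln[(0.25/0.75)/(0.15/0.85)] = ln 1.889 = 0.636.
- Crude SE = √(1/(250·0.25·0.75) + 1/(250·0.15·0.85)) = 0.230.
- Wald power = Φ(0.636/0.2296 − 1.96) = 79.1%.

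The adjusted SE comes from the inverse of the logistic information matrix with intercept, treatment and ICU terms. The common conditional OR is solved so that the treated marginal rate is 15%. The ICU share runs from 20% to 50%.

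| Assumed ICU-vs-ward OR | Adjusted power |
|---|---|
| 1.5 | 79.3–79.4% |
| 2 | 79.7–79.8% |
| 3 | 80.7–80.9% |
| 5 | 82.4–83.0% |

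Across these rows the log OR rises from 0.636 to 0.639–0.706 (OR 1.90–2.03), and the SE rises from 0.230 to 0.230–0.243.

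Two scenarios with an ICU OR of about 6 give:

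- ICU 40%, ward 10%, half each: 79.1% to 83.0%, SE 0.242, conditional OR 2.02.
- ICU 45%, ward 12%, 40% in ICU (control rate 25.2%): 80.5% to 84.9%, SE 0.244, conditional OR 2.08.

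The gain is therefore about 0.2 to 4 points, obtained while the SE rises.

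**The case against.** The strongest reply is that the two statements may be complementary. Neither says it lists the only factor, and several details suggest that a centre is a department. On that reading, stratifying by centre already balances ICU status. This stands as a possibility and reduces the likely harm. It does not remove the contradiction, because the protocol never defines centre.

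A second reply is that covariates are commonly left to the statistical analysis plan, which is not shown. That also stands. A reader might infer that the primary OR is unadjusted and ignores both factors, but section 13.1 is silent rather than negative. The case for naming the model in the protocol rests on something narrower: the protocol itself fixes the OR thresholds for stopping, and a conditional and a marginal OR are different quantities.

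Three further inferences are tempting and unsupported:

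- That leaving out ICU status loses precision or makes the posterior too wide. For a log OR, adjustment does not shrink the standard error; omission pulls the OR towards 1.
- That ICU status is the main prognostic factor. No section says so or gives event rates by setting.
- That ICU patients are all on high-flow oxygen or NIV. Section 5.2 also allows simple oxygen in the ICU.

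Finally, the power figures come from a single fixed-size Wald test, not from this trial's repeated posterior thresholds. They show an order of magnitude only.

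**Conclusion.** The contradiction is real and should be corrected. The synopsis and section 5.3.3 name different stratification factors, and the undefined term centre leaves open whether ICU status is balanced at all.

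If 5.3.3 is applied to centres that mix ward and ICU, the imbalance in ICU share at the 100-patient look has an SD of about 10 percentage points, assuming half the patients are in ICU and no single-setting centres.

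What is at stake for power is small: about 0.2 to 4 points at N=500 under assumed ICU-versus-ward ORs of 1.5 to about 6. This does not threaten the trial. It is a nearly free correction that should be made, and the documents do not support a claim that the primary analysis is wrong as planned.

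**What to change.** - **Section 5.3.3 and synopsis:** state in both that randomisation is stratified by ICU/non-ICU at inclusion and by centre, define centre as a department or a hospital, and confirm that this matches what is programmed in the randomisation system.
- **Section 13.1:** state that the OR behind the posterior thresholds is the treatment coefficient of a Bayesian logistic model that includes the ICU/non-ICU stratum. Use the same model at every interim and at the final analysis, and report the marginal risk difference beside it.

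The cost is a few sentences and model code; setting at inclusion is already needed for the planned subgroup. If a centre can hold both settings, there are up to 21 × 2 = 42 strata, about 500/42 ≈ 12 patients each, which the list must allow for. The downside is that the OR becomes conditional, about 1.9 to 2.1 under the planned effect instead of a marginal 1.9, so the text should say that the 1.05 and 0.95 thresholds refer to that conditional OR.
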